The use of ultra-low RTX could present several advantages over standard low-dose RTX. First, infection risk should be lower, as RTX use is associated with a dose-dependent – although still low – risk of serious infection [17, 18]. Also, shorter infusion duration and less administered drug could lead to less patient burden and perhaps lower risk for infusion reaction [19]. Further, RTX treatment currently is relatively expensive, with costs for low-dose 1 × 1000 mg every six months being in the range of €4000–7000 per year. Although RTX was proven to be cost-effective in patients with an inadequate response to TNFi [20], use of ultra-low doses will further decrease costs and thereby improve cost-effectiveness. A combination of a possible effective dose of 200 mg every six months and expected price reductions due to upcoming availability of a rituximab biosimilar, could result in a bDMARD option availability for under €1000 per patient per year.

The use of an ultra-low dose of RTX might, however, also lead to increased disease activity in the subset of patients whose minimal effective RTX dose is 1000 mg. Therefore, prediction of response to ultra-low-dose RTX would be key to prevent patients from flaring experiencing accelerated joint damage [21]. Interesting baseline (at the moment of considering RTX retreatment) candidates for predicting the chance of good response on an ultra-low dose include higher RTX drug levels, absence of anti-RTX-antibody levels and low peripheral B-cell counts, as it might be hypothesised that these are all indicators for lower RTX need [22].

In conclusion, although the use of ultra-low doses of RTX seems promising, its effects have never been studied in a trial of proper design and size. We therefore aim to perform a RCT to study whether retreatment with one of two ultra-low RTX doses (1 × 200 mg or 1 × 500 mg) is non-inferior to retreatment with the standard low-dose RTX (1 × 1000 mg) for patients with RA who were already successfully treated with standard low-dose RTX. Also, we will analyse whether there are differences between retreatment with ultra-low dose and standard low dose in the occurrence of serious and non-serious adverse events and cost-effectiveness, and we will analyse whether (non-)response to (ultra-)low dose of RTX at six months can be predicted at the moment of initiating retreatment.

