### Objectives

The primary objective of the REDO trial is to compare the difference in efficacy between two ultra-low doses (1 × 200 mg and 1 × 500 mg) and standard low dose (1 × 1000 mg) of RTX retreatment on the change in DAS28-CRP, compared to a pre-specified non-inferiority margin of 0.6 DAS28 points, at three and six months. Therefore, the study has four primary endpoints. Although we are aware that patients are sometimes treated with longer intervals than six months, showing non-inferiority at six months is relevant, for ultra-low RTX dose with at least six-month intervals is still a lower cumulative dose as standard low-dose 1000 mg every 9–12 months.

The main secondary objectives are: to assess the difference in efficacy between the two ultra-low dose interventions for the same outcomes; to compare the proportion of patients with a DAS28-CRP < 2.9 (low disease activity), DAS28-CRP < 2.4 (remission) and remission according to Boolean ACR/EULAR criteria at three-month and six-month follow-up; to assess the between-group differences in the change in functioning (HAQ-DI) and quality of life (EQ5D-5 L); and to compare proportion (cumulative incidence and incidence density) of patients developing (treatment-related) adverse events in each study group over the duration of the study, with special attention to infusion-related adverse events and infections. Furthermore, the cost-effectiveness of both ultra-low RTX doses and the conventional low dose are compared for the six-month study period. For prediction modelling, baseline factors (including RF/ACPA status, CD19+ B-cell count, serum RTX, serum anti-RTX) will be tested for associations with the outcome of DAS28-CRP low disease activity state at six months.

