### Randomisation and blinding

Participants will be allocated to the treatment groups at a ratio of 1:2:2 (1 × 1000 mg vs. 1 × 500 mg vs. 1 × 200 mg). The experimental groups are larger than the control group to increase experience with the lower dosing and with the additional benefit that a larger number of potential predictive factors for response can be studies in multivariate prediction modelling in the ultra-low-dose RTX groups.

Randomisation will be performed using a computerised randomisation procedure and stratified to ensure equal distributions of two possible effect modifiers for response to ultra-low-dose RTX, concomitant conventional DMARD use and RF/ACPA status. Patients will be randomised using block randomisation in variable block sizes (multiples of 5) to more closely achieve the intended allocation ratio and to ensure that the allocation of participants will not be predictable. Patients, physicians, nurses, researchers and data analyst/statistician will be blinded for treatment allocation. The allocation is kept in opaque, sequentially numbered envelopes; envelopes are sequentially assigned by the pharmacist to each next patient. The infusions for the study will be prepared by the hospital pharmacy based on the randomisation number, the physical appearance of the three interventions will be indiscriminate (see below). Unblinding is expected to be rarely necessary (all patients receive RTX and retreatment with 1000 mg is allowed when necessary), but is possible after consulting the coordinating centres pharmacist.

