**Table 1 Tab1:** Total trial sample size at various correlations between endpoints

SD change	r	Sample size 1000 mg arm	Total trial size (5 x sample size in 1000 mg arm)
0.9	0.17	26	130
0.8	0.35	24	120
0.7	0.5	20	100
0.6	0.63	16	80

To protect for a too optimistic correlation, we therefore choose a total trial size of 130 and this is further increased to 140 patients to account for patient drop-out.

Primary analyses will be done per protocol (PP), as this is the most conservative approach for a non-inferiority study. In addition, analyses will be performed on an intention-to-treat basis (ITT). For PP analysis, we will include patients who have received the study medication and completed follow-up of six months or until treatment failure (and last observation of disease activity carried forward).

The primary endpoints will be tested using 95% confidence intervals based on linear regression with the change in DAS28-CRP as outcome, dose group as determinant and baseline values of DAS28-CRP as covariate (ANCOVA).

To find predictors (including age, sex, disease duration, RF/ACPA status, CD19+ B-cell count, serum RTX, serum anti-RTX), patients will be categorised into responders (DAS28-CRP < 2.9 at six months and no treatment failure) and non-responders (all other patients). The absolute number (and thus also proportion) of responders will determine the number of predictors that is admissible for analysis, according to the rule of ten-events-per-variable given that predictors are predetermined. Univariate logistic regression analysis will be performed for the admissible predictive factors, with a deliberately liberal *p* < 0.20 as selection criterion. Univariately significant variables are entered in a full multivariate logistic regression model, that is step-wise reduced until all *p* < 0.20. Internal validation and shrinkage will be performed using a bootstrapping procedure with 1000 repetitions. Performance of the multivariate predictive model will be evaluated using discrimination (area under the receiver operator curve) and calibration (calibration slope, calibration plot and Hosmer-Lemeshow test).

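### The predictor model has no dose or marker-by-dose term, so it can predict outcome on the doses modelled but cannot show which patients need 1000 mg

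*Protocol article*

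**What the plan says.** The Protocol article describes the predictor analysis in four places.

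- **Background, motivation.** Ultra-low dosing might "also lead to increased disease activity in the subset of patients whose minimal effective RTX dose is 1000 mg". The article draws from this that "prediction of response to ultra-low-dose RTX would be key to prevent patients from flaring". It proposes higher drug levels, absent anti-RTX antibodies and low B-cell counts as candidates because "it might be hypothesised that these are all indicators for lower RTX need".
- **Background and Objectives, aims.** The Background closes with "we will analyse whether (non-)response to (ultra-)low dose of RTX at six months can be predicted at the moment of initiating retreatment". In the Objectives, the baseline factors "will be tested for associations with the outcome of DAS28-CRP low disease activity state at six months".
- **Randomisation and blinding.** One reason for the larger experimental groups is that more candidate predictors "can be studies in multivariate prediction modelling in the ultra-low-dose RTX groups".
- **Sample size considerations and statistical analyses.** The candidates are introduced with "To find predictors (including age, sex, disease duration, RF/ACPA status, CD19+ B-cell count, serum RTX, serum anti-RTX". For the outcome, "patients will be categorised into responders (DAS28-CRP < 2.9 at six months and no treatment failure) and non-responders (all other patients". Candidates are screened one at a time at p < 0.20, and those that pass enter a logistic model that is reduced stepwise. Bootstrap shrinkage, discrimination and calibration follow.

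The predictor paragraph names neither dose nor an interaction. The same section does name dose group as the determinant in the primary ANCOVA.

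**The concern.** To need 1000 mg is to do worse on 200 or 500 mg than on 1000 mg. That is effect modification, and it can be seen only by comparing doses. The described model relates responder status to baseline factors alone. A marker that goes with a poor six-month DAS28-CRP on every dose would be selected in the same way as one that matters only at ultra-low doses.

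At stake is the use of the result. If a selected marker is read in the sense of the Background, as an indicator of RTX need, patients could be judged unsuitable for an ultra-low dose although 1000 mg would serve them no better. Discrimination, calibration and shrinkage would not reveal this, because they all assess prediction of the outcome itself and not of a difference between doses.

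**Working it through.** **Step 1. The two questions in one model.** Let M be a marker, and let G = 1 for an ultra-low dose and G = 0 for 1000 mg:

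logit P(response) = a + b·M + c·G + d·M·G

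The marker's slope is b on 1000 mg and b + d on an ultra-low dose. On the logit scale, the dose-need hypothesis concerns d. The described model contains only an intercept and a slope for M.

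- *Fitted in the ultra-low-dose arms:* the slope estimates b + d. A purely prognostic marker (b = log 2, d = 0) and a pure modifier (b = 0, d = log 2) have the same slope there. No sample size separates them.
- *Fitted in all arms without G:* the slope is a mixture of b and b + d, dominated by the ultra-low-dose patients (112/140 = 80%).

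The conclusion is therefore the same whichever arms are modelled.

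**Step 2. Inputs.** From the plan: 140 patients at 1:2:2 give 140 × 1/5 = 28 on 1000 mg and 140 × 2/5 = 56 on each ultra-low dose, so 112 on ultra-low doses; screen at p < 0.20. The article states no power or size for the predictor analysis, so there is no figure of its own to reproduce. Assumed, because the article gives neither: response of 60, 70 or 80% at the average marker value, and an odds ratio of 1.5 or 2.0 per SD of one standardised marker. The illustration has no main effect of dose and treats the two ultra-low doses alike.

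**Step 3. Simulation.** 3,000 trials per setting, Wald tests. Entries are the percentage of trials in which the term passes.

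| Marker | Response | Marker only, all arms, p < 0.20 | Marker only, ultra-low arms, p < 0.20 | Interaction, p < 0.20 | Interaction, p < 0.05 |
|---|---|---|---|---|---|
| Prognostic, OR 1.5 | 60% | 85.1 | 78.5 | 21.1 | 3.8 |
| | 70% | 80.5 | 73.3 | 20.2 | 3.8 |
| | 80% | 72.5 | 65.7 | 18.9 | 3.1 |
| Prognostic, OR 2.0 | 60% | 99.4 | 98.3 | 20.6 | 3.9 |
| | 70% | 99.1 | 97.7 | 20.0 | 3.1 |
| | 80% | 97.3 | 94.0 | 20.3 | 3.3 |
| Modifier: OR 1.0 on 1000 mg, 2.0 on ultra-low | 60% | 96.2 | 98.5 | 59.2 | 32.0 |
| | 70% | 94.9 | 97.8 | 56.0 | 30.3 |
| | 80% | 90.3 | 94.4 | 47.9 | 22.6 |

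In the ultra-low-dose arms, the OR 2.0 prognostic marker (94.0-98.3%) and the modifier (94.4-98.5%) are selected equally often, as Step 1 predicts. The interaction test flags the prognostic marker at about its nominal rate (19-21% at p < 0.20) and the modifier in 48-59%. At p < 0.05 it finds the modifier in only 23-32%.

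**Step 4. Room for parameters.** With three dose levels, the three Background markers and all their interactions need 2 + 3 + 6 = 11 terms. With one dose term they need 1 + 3 + 3 = 7. At 60, 70 and 80% response, 140 patients give 84, 98 and 112 responders, so the plan's ten-responders rule allows 8, 9 and 11 terms. Counting non-responders instead (56, 42 and 28) would allow 5, 4 and 2. Eleven terms are too many in most of these settings; seven fit the plan's rule but not the stricter count.

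**The case against.** The strongest reply is that the formal aims contain no contrast between doses. The Objectives ask for association with low disease activity at six months, and the Background's closing aim is prediction of response. For either, a marker that predicts non-response among patients on an ultra-low dose is a legitimate predictor, even if it predicts equally well on 1000 mg. This stands. A reader might take the selection rates above for an error rate; they are the power to detect a real association, under assumed inputs.

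A reader might also infer that 200 and 500 mg are pooled and that the 1000 mg arm goes unused. The article does not say so. The statistical section does not name the arms modelled, the Background's wording can include the standard low dose, the predictor list is open, and the full protocol is a supplement not shown here. The point does not depend on these inferences: univariate screening of baseline factors followed by stepwise reduction does not produce an interaction, whichever arms are used.

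It can further be said that eligibility already shows how each patient did on a standard dose (see Patients). That is useful history. It is not a concurrent control, because some patients may lose response on 1000 mg as well.

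Finally, an interaction analysis is weak with 28 patients on 1000 mg. This also stands, and it limits what the fix may claim.

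**Conclusion.** The point holds in a limited form. The Background raises a dose-need hypothesis for three markers, and the described model does not test it. The model does serve the association aim in the Objectives, so the documents do not support a reading that it fails its stated objective or mislabels predictors of ultra-low-dose response. What it cannot support is a statement about who needs 1000 mg.

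That conclusion is structural (Step 1) and needs no assumed figure. The sizes do: with an odds ratio of 2.0 per SD and 60-80% response, the planned screen selects a prognostic marker and a true modifier about equally often in the ultra-low-dose arms, and an interaction test finds the modifier in about 23-32% of trials at p < 0.05.

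The analysis is secondary, and the four primary non-inferiority tests are unaffected. This is a cheap improvement.

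**What to change.** 1. **Force randomised dose into the prediction model**, exempt from screening and stepwise removal, so that predicted probabilities are dose-specific.
2. **Add a separate analysis, labelled exploratory**, of marker-by-dose interactions for serum RTX, anti-RTX and CD19 count in all three arms. Use one dose term (log dose, or ultra-low versus 1000 mg) to limit parameters. Report the interaction estimates and the predicted between-dose differences in response by marker level, with confidence intervals.
3. **Do not treat a non-significant interaction as proof that a marker is only prognostic.** Under the Step 3 inputs, such a rule at p < 0.05 would misclassify the modifier in about 68-77% of trials (100 minus 32.0, and 100 minus 22.6).
4. **State in the plan** that predictors from the main model are prognostic and do not by themselves identify patients who need 1000 mg.

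The cost is analysis wording only: the Assessments section describes baseline blood sampling without restriction by arm. The downside is imprecision. With about 28 patients on 1000 mg the intervals will be wide, and the exploratory label has to be carried into the report.

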**Methods/Design:**

REDO is an investigator driven six-month pragmatic, double-blind, randomised controlled non-inferiority trial on the effects of ultra-low-dose RTX (1 × 500 or 1 × 200 mg) compared to standard low dose (1 × 1000 mg) in RA patients who are being retreated with RTX. A total of 140 RA patients, having reached low disease activity (DAS28CRP < 2.9) after the previous RTX infusion and DAS28CRP < 3.5 at moment of retreatment, are randomised in a ratio of 1:2:2 to 1 × 1000 mg, 1 × 500 mg or 1 × 200 mg. The primary objective is testing non-inferiority of the ultra-low-dose vs. standard low-dose RTX, by comparing mean change in DAS28CRP from baseline to six months to the non-inferiority margin of 0.6. Secondary outcomes over the same period are: function; quality of life; safety; costs; and pharmacokinetics and dynamics as process measures.

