### Patients

Inclusion criteria for patients in this pragmatic study are as non-restrictive as possible. This is based on the underlying principle that the results of this trial should be generalisable to all RA patients who are doing well on their RTX treatment. We therefore include RA patients fulfilling either 2010 EULAR/ACR RA [30] and/or 1987 RA [31] criteria and/or having a clinical diagnosis of RA according to the treating rheumatologist, at any time point between start of the disease and inclusion.

Patients are eligible if they were treated at least once with regular low-dose RTX treatment in the last 18 months for RA, so in a dose of 1 × 1000 mg, 2 × 1000 mg or 2 × 500 mg, and had received no other bDMARDs after the last RTX dose. Patients treated with innovator RTX (MabThera®) as well as authorised RTX biosimilars in similar doses as conventional RTX will also be included.

It is somewhat difficult to operationalise the criterion that patients need to be doing well enough on RTX because of the variety of retreatment strategies that are used in clinical practice. We decided on at least six months of stable, low-disease activity after the last RTX infusion (operationalised by either DAS28-CRP < 2.9/DAS28-ESR < 3.2 or judgement of low-disease activity by a rheumatologist) and a current DAS28-CRP ≤ 3.5/DAS28-ESR ≤ 3.8. The latter criterion is added, because patients are often not retreated at fixed intervals, but are retreated either based on treat-to-target or on demand when disease activity increases. However, we do not want to generalise to patients being treated only when they flare severely, as it has been shown that the optimal strategy for RTX retreatment (although not completely clear yet) is either fixed interval or treat-to-target, but not treated only on demand. Also, a high SD in disease activity at study start would increase the required sample size.

Further inclusion criteria are chosen to ensure that we are able to study the participants and to measure the outcomes: patient informed consent; age ≥ 18 years and mentally competent; life expectancy > 6 months; no planned relocation out of reach of study centre; and able to read and communicate well in Dutch.

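### The prediction model's predictor count is tied to the number of responders; it should be tied to the smaller outcome class, which is likely to be the non-responders

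*Protocol article*

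**What the plan says.** The prediction model is described in the protocol article under Sample size considerations and statistical analyses. A responder has DAS28-CRP below 2.9 at six months and no treatment failure; everyone else is a non-responder. The size of the candidate set is then fixed: "The absolute number (and thus also proportion) of responders will determine the number of predictors that is admissible for analysis". The yardstick for turning that count into a number of predictors follows directly, namely "according to the rule of ten-events-per-variable given that predictors are predetermined". The candidates are introduced as "including age, sex, disease duration, RF/ACPA status, CD19+ B-cell count, serum RTX, serum anti-RTX", which names seven in an open list. The admissible candidates go through univariate screening at p < 0.20 and stepwise reduction. Bootstrap validation and shrinkage with 1000 repetitions follow.

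Two other sections bear on the count. Randomisation and blinding gives the 1:2:2 allocation and places the work in "multivariate prediction modelling in the ultra-low-dose RTX groups". Patients requires "at least six months of stable, low-disease activity after the last RTX infusion", met by a DAS28 threshold (2.9 for DAS28-CRP) or by the rheumatologist's judgement, together with a current DAS28-CRP of at most 3.5.

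**The concern.** A logistic model is symmetric in how the outcome is coded: calling response or non-response the event changes only the signs of the coefficients. The information for estimating them is limited by whichever class is smaller, and the ten-per-variable rule is meant for that class. A rule that counts responders is right only while responders make up no more than half of the patients. Above half it works backwards, because each extra responder earns more predictors while one fewer non-responder is left to learn from.

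The population is selected for doing well on rituximab, and the 2.9 cut that defines response is also the DAS28-CRP threshold for low disease activity in the entry criteria. Responders are therefore likely to be the larger class.

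Two uses of the model are at stake. The Background treats prediction as key to sparing patients who need the full 1000 mg from flaring on less. Randomisation and blinding partly justifies the larger ultra-low-dose arms by the number of predictive factors that can be studied. A rule that overstates this number overstates that benefit and weakens the model.

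**Working it through.** **Inputs.** The total is 140 ("we therefore choose a total trial size of 130 and this is further increased to 140 patients to account for patient drop-out"), allocated 1:2:2. The two ultra-low-dose arms hold 140 × 4/5 = 112. The rule is ten events per predictor, with seven predictors named. The document states neither an expected responder share nor a resulting number of predictors, so there is no printed predictor count to reproduce.

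**Check of the trial size.** The chosen row of Table 1 has SDchange 0.9, so r = 1 − 0.81/(2 × 0.49) = 0.173. The 1000 mg arm needs 1.5 × (1.96 + 1.645)² × 0.49 × (1 − 0.173²)/0.36 ≈ 25.7, that is 26, and 5 × 26 = 130. This matches the table, so the denominators below stand on the plan's own figures.

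**Formulas.** With R responders among N patients and p = R/N:
- written rule: floor(R/10)
- smaller-class rule: floor(min(R, N − R)/10)
- excess before rounding, for p > 0.5: R/(N − R) = p/(1 − p)

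**Results over an assumed p** (written rule vs smaller-class rule; the last column is for the 112):

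| p (assumed) | p/(1−p) | 112 patients: R / non-R | Predictors, 112 | Predictors, 140 | Non-responders per admitted predictor |
|---|---|---|---|---|---|
| 50% | 1.0 | 56 / 56 | 5 vs 5 | 7 vs 7 | 56/5 = 11.2 |
| 60% | 1.5 | 67 / 45 | 6 vs 4 | 8 vs 5 | 45/6 = 7.5 |
| 67% | 2.0 | 75 / 37 | 7 vs 3 | 9 vs 4 | 37/7 = 5.3 |
| 75% | 3.0 | 84 / 28 | 8 vs 2 | 10 vs 3 | 28/8 = 3.5 |
| 80% | 4.0 | 90 / 22 | 9 vs 2 | 11 vs 2 | 22/9 = 2.4 |

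At 80%, 112 × 0.8 = 89.6. Rounding up to 90 responders gives 9 predictors by the written rule and rounding down to 89 gives 8; the smaller class supports 2 either way. Below 50%, responders are the smaller class and the two rules agree.

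**A result that needs no assumed share.** The written rule admits seven predictors once R ≥ 70. Among 112 patients, non-responders are then at most 112 − 70 = 42. That is at most 42/7 = 6 per predictor, and it supports floor(42/10) = 4. Among all 140, non-responders are at most 70, so seven are supportable only at exactly 70/70; at 71/69 the smaller class supports 6.

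**Is a majority of responders plausible?** The sample size section uses SD 0.7 and, through its formula for SDchange, the same SD at baseline and follow-up. Taking DAS28-CRP at six months as normal with that SD and an assumed mean, the share below 2.9 is 50% at a mean of 2.9, 67% at 2.6 and 80% at 2.3. Treatment failures lower it: with 10% failures (also assumed, and independent of the score), a mean of 2.6 gives about 60% and a mean of 2.8 about 50%. A majority is likely over this range, but not guaranteed.

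**The case against.** The strongest reply is that no responder rate appears anywhere in the document. Patients may enter with DAS28-CRP between 2.9 and 3.5, already above the responder cut. Low disease activity may be certified by judgement, and every treatment failure counts as a non-responder. The planning assumption of no true difference concerns mean DAS28 between doses and does not fix the responder share. All of this stands: a majority of responders is an inference, and at 50% or below the rule does no harm. A reader might take two to four times too many predictors as the size of the error, but that holds only for an assumed share of 67% to 80%.

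A second reply is that the same paragraph has safeguards: predetermined predictors, a cap applied before screening, bootstrap shrinkage, and checks of calibration and discrimination. These count in the plan's favour, and it would go too far to say that the model will be overfitted. Shrinkage reduces optimism after fitting; it does not put the cap on the right class.

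Third, the plan caps the number of predictors and never promises to fit all seven. The modelling set is not fully settled either: the end of the Background speaks of predicting response to the low dose as well as the ultra-low doses. Both points are fair. The seven-predictor result is therefore conditional on the rule admitting seven, and both 112 and 140 are shown.

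A reader might also infer that baseline DAS28-CRP and dose are wrongly left out, or that B-cell counts and drug levels could stand in for dose. The document does not support either. The list is open, and the article says that the full protocol is supplementary material. Baseline markers are independent of a randomised dose except by chance.

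**Conclusion.** The point holds in limited form. The rule as written counts the wrong class whenever responders exceed half of the modelled patients, and the entry criteria make that likely. The excess is about p/(1 − p), so its size depends on a responder share that the document does not give. One consequence needs no assumed share: in the ultra-low-dose set, any result that lets in all seven named predictors breaches the ten-per-variable standard that the plan invokes.

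The reach is one secondary analysis. The four primary non-inferiority comparisons do not depend on it.

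**What to change.** In the prediction paragraph, replace the reference to the number of responders with: *the smaller of the numbers of responders and non-responders*. Count it in the set of patients in which the model is fitted, and apply it to the predetermined predictors. The change is one phrase and can be made before unblinding.

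The cost is that fewer predictors can be examined. At an assumed two-thirds responder share in 112 patients, the number falls from 7 to 3. If responders turn out to be half or fewer, the change alters nothing.
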